#### 3.8.5.2.2. Passive data through Oura Ring

During the Screening and Baseline Visit, a member of the study team will familiarize participants with the Oura Ring and mobile application. Participants will use the credentials of a de-identified email account to log in to the Oura Ring application. Participants will be asked to wear the Oura Ring throughout their involvement in the study (3-week baseline + IPP treatment). Table 1 provides details of the parameters collected by the Oura Ring.

**Table 1: Description of the Oura Ring wearable device and data collection**

| Device    | Description                                                                                                                                                                                                                                                                                                                                           | Data Transfer                                                                                                                                                                                                                                                                                                                                                                                                                                                                                                                                                                                            | Data elements                                                                                                                                                                                                                                                                                                                                                                                                                                                                                                                                                                                            |
|-----------|-------------------------------------------------------------------------------------------------------------------------------------------------------------------------------------------------------------------------------------------------------------------------------------------------------------------------------------------------------|----------------------------------------------------------------------------------------------------------------------------------------------------------------------------------------------------------------------------------------------------------------------------------------------------------------------------------------------------------------------------------------------------------------------------------------------------------------------------------------------------------------------------------------------------------------------------------------------------------|----------------------------------------------------------------------------------------------------------------------------------------------------------------------------------------------------------------------------------------------------------------------------------------------------------------------------------------------------------------------------------------------------------------------------------------------------------------------------------------------------------------------------------------------------------------------------------------------------------|
| Oura Ring | The Oura Ring is a smart biosensor device that is worn on the finger and passively collects physiological parameters and information on sleep and activity levels of an individual. It is considered a smart-ring because it uses advanced sensor technology to allow for precise, personalized health insights about one's body (see Data Elements). | Participants will download the Oura app to their smartphone and log on using their de-identified study ID details. The Oura Ring must be connected to the smartphone via Bluetooth to regularly sync data. The Oura Ring collects data locally and sends it to the mobile app when synchronized. Once the Oura App is connected to the internet (e.g., wifi or phone data), the data will be uploaded to the remote Oura server. For data analysis, only authorized research members will have access to the data collected by Oura Ring through its respective application programming interface (API). | 
Some of the physiological and activity data extracted from the Oura Ring include:
 
 
• Heart rate
 
• Heart rate variability (HRV)
 
• Respiration rate
 
• Daily activity levels
 
• Oxygen saturation (SpO2)
 
• Body temperature variability (delta)
 
• Readiness score
 
• Calories
 
 
Sleep data:
 
 
• Sleep stages: deep sleep, rapid eye movement (REM), light sleep and awake periods
 
• Sleep score
 
• Nap detection
 
 |

The following steps will outline the data collection process of the Oura Ring device:

1. The account and device will be set up by a study team member with a unique de-identified study ID and email. The data will be anonymous and only identifiable by select research members with access to the master log.
2. Metrics extracted by the Oura Ring will be collected and synchronized to the Oura smartphone app (via Bluetooth) and the Oura server (via secured internet connection). Oura has its own secure server where the data will be stored separately from active (REDCap) data.
3. The research team will have access to the secured Oura Application Programming Interface (API) to extract data from its respective server. The API will securely connect to the respective servers to extract de-identified passive data. The de-identified data will be available to the research team for analysis. The data will be securely extracted using the Oura API and stored on an external encrypted and password-protected hard-drive, accessible to only select members of the research team. The data extraction program will be executed weekly so that data will be extracted and stored regularly.

Since participants who use the Oura Ring for this study will be undergoing different treatments (rTMS, IVK or ECT), there is a possibility that wear times may vary slightly according to the duration of clinical treatment, and this will be the same for REDCap data collection. The device will be returned to the study team at the end of the last treatment session. All returned rings will be cleaned, sanitized, and allocated a new de-identified study ID before being given to another participant.

### **3.9. Reimbursement**

There are no reimbursement costs associated with this study, as all study activities are taking place alongside IPP clinic treatment.

### **3.10. Quality Assurance**

Methods for quality assurance will be strictly observed. A start-up meeting involving all study site research staff, co-investigators, and partners will be held prior to the launch of the study.

Further training (e.g., REDCap, Oura sizing and use) will be held prior to commencing the study. During training, great care will be taken to fully explain the clinic and study procedures and case report form (CRF) completion.

## **4. DATA MANAGEMENT**

Active data collected through the REDCap platform will be stored on the REDCap server (accessible to the study team). Demographic and medical history data collected as part of the IPP intake process will be stored on the UHT Network folder and patients' electronic health records (EHRs; accessible only to the clinical team). Paper questionnaire forms used as part of clinical care will be stored in a locked cabinet accessible only to the clinical team and will be securely destroyed after being entered into the patient-participant's REDCap form and EHR. The Oura Ring will collect de-identified passive and continuous data through wearable technology. The data will be collected on the respective app, wherefrom it will be transferred to and stored on its respective server. The digital platform will be set up to comply with the protection of privacy of the participant. We will use the Oura API to extract available data from their servers and store on an external encrypted and password-protected hard-drive. Data collected from the Oura Ring and REDCap will be independent from one another and will only be linked for analysis. No personal health or clinical information will be shared with Oura.

A designated research team member will ensure that the REDCap and Oura platforms are working properly by surveilling the platforms and data on a weekly basis. The clinical team will be notified of any participants with missing data over the past week (3 of the past 7 days) so they can communicate with the patients at the next treatment session. Participants will be referred to the research team to troubleshoot any technical issues, as needed. Participants will be able to contact the Study Coordinator ([name], [[contact]](mailto:[contact])) with any study-specific questions throughout the study duration, or may contact the study-specific email ([[contact]](mailto:[contact])) - which is monitored daily by the research team - for technical assistance.

### **4.1. Security and Privacy of the Study Data**

#### ***4.1.1. Oura Ring Wearable Device***

A subset of participants will use the Oura Ring wearable device to collect passive data (Section 3.6.2). The device and its respective app will have a specific user ID and de-identified email that will be set up by the research team so that the participant remains de-identified on this platform. Data collected from the Oura Ring wearable device will be made accessible through the Oura API. Each participant's de-identified data will be exported and stored on an external encrypted and password-protected hard-drive and the data will only be associated with a participant identification number.

Each device will collect parameters related to mental health and wellness, such as heart rate variability (HRV), sleep metrics, and the Oura Activity Score. Additionally, the Oura device and mobileapp are independent from the web-based REDCap platform; therefore, data from one platform are not linked or related to any other platform except through the de-identified ID assigned to the participant.

No personal information will be collected through the Oura digital platform and only authorized members of the project will be able to access the data. Study data will be stored for a minimum of seven years and may be used for other research or analyses by the investigators, or by other researchers. Future studies where this data will be used or shared will be subject to REB approval.

#### ***4.1.3. REDCap***

REDCap (<https://www.project-redcap.org>) is supported by the Applied Health Research Centre (AHRC) at UHT. REDCap is an open-source, web-based clinical data management and electronic data capture system and database. The system is developed and managed in compliance with UHT privacy, the Health Insurance Portability and Accountability Act, the Personal Information Protection and Electronic Documents Act (PIPEDA), and Food and Drug Administration 21 Code of Federal Regulations Part 11 regulations, providing functions such as defined user roles and privileges, user authentication and encryption for in-transit data, de-identification of protected health information, and comprehensive auditing features to record and monitor access and changes to data. This system will be used to collect and store active

(CRFs and self-report questionnaire) data and for the query and export of datasets for statistical analysis and modeling.

Access to REDCap will be protected through a secure web portal and protected by multiple levels of authentication and authorization. Project Coordinators will be assigned the project administrative privileges for study configuration, data collection management, and quality control. Participants will complete self-report mental health questionnaires in line with their clinical treatment protocol; upon acceptance to the study, the clinical team will enter patient-participants' responses into REDCap after each treatment session (based on CRFs completed as part of clinical care). Active data will be stored on the REDCap server and will be linked by the de-identified ID for final analysis. Only Project Administrators will be granted access to download the data from the REDCap server for analysis.

During data analysis, de-identified data will be provided to the analysts. This will be achieved using a two-zone approach. The two-zone approach divides study team members into two groups; identified and de-identified. As the names suggest, the identified group will have access to identified (i.e. demographic data) and de-identified information and thus is able to re-identify the data to provide data management, quality and data linkage functions (on active and passive data) whereas the de-identified group will only have access to the de-identified information. This will ensure that the data analysts of the team only have access to de-identified data but will not have access to any of the participant's identifiers to protect participant privacy.

## **5. DATA ANALYSIS METHODS**

### **5.1 Statistical Analysis**

We will assess the feasibility of digital interventions using descriptive statistics with counts and proportions for categorical data and means and standard deviations (parametric) or median and interquartile range (non-parametric), as appropriate, for continuous data. The proportion lost to follow-up will be estimated along with a 95% confidence interval. The upper 95% confidence limit should not exceed 20% to proceed. The proportion compliant with the protocol, including treatment compliance as well as study completion and complete data on clinical outcomes (i.e., the per-protocol group) will be estimated with a 95% confidence interval. For validity, this

should be fairly high so that the lower 95% confidence limit is  $> 80\%$ . Group- (*t*-tests, ANOVA, ANCOVA, correlation, regression) and individual- (multilevel modeling) level biostatistics will be used to identify and quantify changes in active (anxiety and depression symptoms) and passive (biometrics) data across treatment arms and over time.

Machine learning and advanced analytics (e.g., dimensionality reduction, statistical relevance or multi-view bi-clustering) will also be used to fuse the passive physiological data with the active questionnaire data. More specifically, passive data is effective at identifying behaviours and trends in activity but is poor in measuring people's internal states, motivation, and attitude, whereas active data is the opposite. Developing a methodology for integrating the two data sources can mitigate their respective weaknesses. The passive physiological data will be fused with the active data collected by the REDCap platform. The motivation to fuse active and passive data includes the cross-validation and improvement of measurements, the explanation of human behaviour, and novel opportunities to improve causal inference in experimental settings.

The active data will serve as a ground truth to validate the passive data from the mobile phone for monitoring a “depressed experience”. We will use generalized machine learning models to detect and predict distress and depression among participants and develop personalized temporal machine learning models for personalized application. This will involve creating predictive models based on a participant’s data and implementing the model suited for the participant. This proposal will be an iterative process. To combat missing data, filtering, and encoders can be used to interpolate and predict the expected data accordingly.

During the analysis, we will extract features from the passive physiological data for better representation. Trends, classifications and relationships will be determined using different machine learning techniques. Implementations of pre-processing, feature extraction and machine learning will be conducted in a numerical program for efficient and powerful processing that will achieve impactful results.

## 5.2. Personal Digital Phenotype Analysis and Generation

Our goal is to have a systematic investigation of DPP with an emphasis on robustness for long-term utility. We envision the DPP to be represented as a multi-dimensional vector composed of passive and active data, where each profile is unique to one another. To do so, we propose a Statistics, Information Theory, and Data-driven (SID) pipeline to develop the foundation of the DPP. The proposed SID pipeline is encapsulated in Figure 3.

[figure not shown]

Figure 3: Block diagram representation of the proposed SID pipeline

DPP will be created through the use of SID, and will be a representation for each individual user. Once the DPP is created, we enhance the analysis by proposing the personalized digital phenotype profile (pDPP) where we develop individual models for each person by incorporating their physiological data together with their self-reported affective states collected from questionnaires. Once the personal profile/model has been constructed, physiological data (such as that collected from the Oura Ring) can be used to provide insight into a person's affective state, even without any active data. The pDPP will be used for long-term utility where we monitor the changes in physical and behavioural health of an individual participant. The application of pDPP could allow for insights into mental well-being in a non-intrusive way that can improve mental health care and responses to stress.

## 5.3. Interpretation of the Personal Digital Phenotype Profile

Our goal is to have a systematic investigation of pDPP with an emphasis on robustness for long-term utility. We envision the pDPP to be represented as a multi-dimensional vector composed of passive and active data, where each profile is unique to one another. We will use analytical techniques such as robust principal component analysis (RPCA) to represent the data. In addition, RPCA decomposes the matrices to low- and sparse-rank representation where the

low-rank representation can be considered the outliers and sparse-rank can be considered as the concise representation of the pDPP vector. We plan to develop an algorithm to analyze the low-rank representation for anomaly detection where new additional samples are added (passive or active data) or when the pDPP baseline varies past an accepted threshold, an alert of potential change in physical and behavioural health can be announced.

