### ***2.2.1 Personal Digital Phenotype Profile Definition***

We propose the definition of digital phenotype profile (DPP), which calculates an individual's baseline and continuously monitors for changes in DPP characteristics derived from mathematical models. Digital phenotype profile (DPP) is a representation of a user's physical and behavioural health using the baseline data collected at the beginning of the study as reference. The models are then fine-tuned with the continuous incoming data streams. However, variations of the model representations require further investigation to ensure its accuracy and robustness. This work investigates the statistical aspect of the analysis pipeline to offer a robust DPP representation. Specifically, the use of robust principal component analysis (RPCA) to extract sparse representation. The DPP is developed through our Statistical, Information Theory,

and Data-driven (SID) pipeline, then is represented through the sparse-rank matrix using RPCA. Once the DPP representation has been created, we additionally enhance this definition by proposing the term pDPP as a personalized version of the DPP, where we use collected longitudinal data to monitor the changes in physical and behavioural health of an individual participant.

The process of digital phenotyping involves building a mathematical model using the active and passive data collected from each participant. An individual model is built for each person by incorporating their physiological data together with their self-reported affective states collected from questionnaires. Once the personal profile/model has been constructed, physiological data (such as that collected from the Oura Ring) can be used to provide insight into a person's affective state, even without any active data. In the long run, such models could allow for insights into patients' mental well-being in a non-intrusive way that can improve mental health care and responses to stress.

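### Protocol 5.3 reverses the roles of the two robust PCA components, so the profile and the anomaly step are each assigned to the wrong matrix

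*Protocol*

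**What the plan says.** Constructing personalized digital phenotype profiles (pDPPs) is a secondary aim (section 2.2) and a listed secondary outcome (section 3.7, item c). Two sections of the protocol say how the profile is represented.

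- **Section 5.3** names the method: "We will use analytical techniques such as robust principal component analysis (RPCA) to represent the data". It describes the split: "RPCA decomposes the matrices to low- and sparse-rank representation". It then gives each part a role: the "low-rank representation can be considered the outliers and sparse-rank can be considered as the concise representation of the pDPP vector". The next step follows from that: "We plan to develop an algorithm to analyze the low-rank representation for anomaly detection". A second route to an alert is added: "when the pDPP baseline varies past an accepted threshold, an alert of potential change in physical and behavioural health can be announced".
- **Section 2.2.1** describes "the use of robust principal component analysis (RPCA) to extract sparse representation" and says that the DPP, once developed, "then is represented through the sparse-rank matrix using RPCA". The same section states the purpose: the DPP "calculates an individual's baseline and continuously monitors for changes in DPP characteristics derived from mathematical models".

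Section 5.3 therefore makes the full assignment (low-rank as outliers, sparse as profile). Section 2.2.1 makes only the second half. It does not mention the low-rank part, outliers or anomaly detection.

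**The concern.** In RPCA the data matrix is split so that regular, recurring structure goes into the low-rank part and a small number of gross departures go into the sparse part. Keeping such departures out of the low-rank part is what makes the method robust. Section 5.3 states the opposite as a description of the method, and then names the low-rank part as the input to the anomaly algorithm.

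Two things are at stake. First, section 2.2.1 wants a profile that captures an individual's baseline, and a profile stored in the sparse matrix would not contain it. Second, a search of the low-rank part for anomalies looks where isolated ones have been removed. This is an incorrect statement in the protocol about a named outcome, and not a detail left open for an analysis plan.

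**Working it through.** **Inputs from the protocol.** The method is RPCA, with one low-rank and one sparse part (5.3). Roles: low-rank = outliers, sparse = pDPP (5.3); sparse = DPP (2.2.1). Anomaly detection is on the low-rank part (5.3). Purpose: an individual's baseline and changes in it (2.2.1). The protocol gives no matrix dimensions, rank, outlier frequency or alert threshold, and there is no stated figure to reproduce.

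**Definition.** RPCA writes M = L + S and minimises ‖L‖\* + λ‖S‖₁. The nuclear norm ‖L‖\* favours a few shared patterns, and the L1 norm ‖S‖₁ favours a few non-zero cells. A pattern that recurs over many rows and columns is cheap to hold in L. A lone spike is cheap to hold in S. The roles follow from the objective function.

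**Illustration.** All settings below are assumptions. Data are M = L₀ + S₀ + noise, with L₀ of low rank (the true pattern) and S₀ zero except for a small share of corrupted cells. The fit is principal component pursuit with λ = 1/√max(m, n); for 60 × 12 this is 1/√60 = 0.129. Two measures are used:

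- the correlation of each fitted part with L₀, taken over all cells;
- AUC = [R₁ − n₁(n₁+1)/2] / (n₁n₀), where R₁ is the rank sum of |fitted value| in the n₁ corrupted cells and n₀ is the number of clean cells.

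Main setting (60 days × 12 features, rank 2, 4% corrupted, 100 runs):

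| | Low-rank L | Sparse S |
|---|---|---|
| AUC for corrupted cells | 0.48 | about 1.00 |
| Correlation with true pattern | 0.99 | 0.13 |

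Other settings (30 runs each, corrupted cells shifted by ±5):

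| Rows × features, rank, % corrupted, noise SD | corr(L, L₀) | corr(S, L₀) | AUC from S | AUC from L |
|---|---|---|---|---|
| 60 × 40, 2, 5%, 0 | 1.000 | −0.001 | 1.00 | 0.494 |
| 60 × 12, 2, 5%, 0 | 0.994 | 0.038 | 1.00 | 0.498 |
| 60 × 40, 2, 5%, 0.1 | 0.999 | 0.022 | 1.00 | 0.492 |
| 60 × 12, 2, 5%, 0.1 | 0.992 | 0.110 | 1.00 | 0.494 |
| 60 × 40, 3, 10%, 0.1 | 0.999 | 0.025 | 1.00 | 0.498 |

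In every setting the low-rank part is at chance for isolated deviations, and the sparse part carries little or none of the underlying pattern.

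**Sustained change.** Isolated spikes are only one kind of change. With 60 × 12, rank 2, noise SD 0.1 and a shift of 1.5 in 6 features over the last 30 days (100 runs), about 92% of the shift goes into L and 8% into S. That is 0.92 × 1.5 = 1.38 in L and 0.08 × 1.5 = 0.12 in S. A lasting change therefore shows in the low-rank part.

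**The case against.** The strongest reply is that the damage is smaller than the reversal suggests. Several parts of it stand.

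- **The alert is not blind.** A reader might infer that the alert could not detect any departure from baseline. The text does not support that. The second trigger watches the pDPP, which the protocol places in the sparse part, and isolated deviations do appear there. The first trigger watches the low-rank part, which takes up most of a sustained shift. What fails is the stated anomaly step for isolated deviations.
- **The matrix is not defined.** The simulation takes one person's days by features. If participants were pooled, the low-rank part would be what they share and the sparse part could be what is person-specific. In an assumed pooled example (60 persons × 40 features, 5% individual deviations), S correlated 0.996 with those deviations and L 0.01. The protocol does not state this reading, and section 5.2 describes individual models for each person. Even under pooling, the low-rank part would be common background and not outliers. The pipeline diagram (Figure 3) and the cited methods paper could not be consulted.
- **The simulation plants what RPCA is built to separate.** This is true. It shows the direction of the error and not its size in this study.
- **The wording is provisional.** Section 5.3 offers RPCA as one example technique and the algorithm is still to be developed. That makes correction easy but does not make the assignment right.
- **The alert is not an outcome.** Section 3.7 lists only construction of the profiles, and no study procedure acts on an alert.

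**Conclusion.** The point holds in a limited form. Section 5.3 states the roles of the RPCA components the wrong way round and builds the anomaly step on that. Section 2.2.1 shares the half that puts the profile in the sparse matrix. As written, the profile would not hold the individual baseline that section 2.2.1 says it calculates, and the anomaly step on the low-rank part would miss isolated deviations while still being able to show sustained shifts.

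The direction follows from the definition of RPCA. The magnitudes depend on assumed dimensions, rank, outlier share and noise, and on a days-by-features matrix for each person.

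A reader might also infer that the study's main conclusions are at risk. They are not: the primary feasibility outcome and the sample size do not depend on RPCA. Because a named secondary outcome would be built incorrectly if the text were followed, the severity is moderate.

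**What to change.** In sections 5.3 and 2.2.1:

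1. Define the DPP and pDPP baseline from the low-rank component.
2. Detect isolated anomalies from the sparse component, or from the residual of new days projected on the low-rank subspace.
3. Assess sustained change as a shift in the low-rank component between time windows.
4. Replace *sparse-rank* with *sparse*, since sparsity describes entries and not rank.
5. If a person-specific deviation from a pooled background is intended instead, say so and define the matrix (what the rows and columns are). Do not call the low-rank part outliers.

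The cost is wording in two sections. No data collection, sample size or resource changes, and modelling is retrospective, so the correction can be made before analysis.
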